### Outcomes

The primary outcome is the difference in postoperative length of stay between the intervention and control groups. Secondary outcomes include adherence to protocol metrics during the intervention period; comparison of morbidity, mortality rates, hospital readmissions, and assessment of PROMs and PREMs between the intervention and control group at 30 days and up to 6 months after CABG.

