### Follow-up

All patients included in the analysis will be followed up at 30 days and 6 months post-discharge, via telephone call, to assess hospital readmission rates, morbidity, patient-reported experience measures (PREM) [25,26], patient-reported outcome measures (PROM) adapted from the model by Ben-Ali et al. [27], as outlined in fil Table in S2 Table, and mortality.

Variables from the PREM and PROM instruments are collected in electronic forms dedicated to the REPLICCAR III project in REDCap, via telephone interviews conducted by the study’s technical research trainee and trained undergraduate research students [28]. All personnel were trained and instructed by the coordinating center to perform these activities, under the supervision of each responsible investigator. To mitigate loss to follow-up, several strategies were implemented, including providing patients with informational leaflets alongside the informed consent form and before hospital discharge, with follow-up call schedules and the names of study personnel. Information is reinforced to patients and their relatives during hospitalization.

An independent adverse event committee will follow up patients to track and report any adverse events and evaluate their potential relationship to the study design.

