### Database

The Cardux platform (https://cardux.net/, Fig 3) and REDCap [30] will be used for secure data storage, accessible by username and password for both study phases. Variables collected during the study will be based on insights from the REPLICCAR II project [31], addressing data related to patient demographics (e.g., gender, age, comorbidities), pre-, intra- and postoperative phases (e.g., clinical exam results, use of cardiopulmonary bypass, need for blood transfusion, complications), as well as hospitalization metrics (e.g., length of surgical procedure, postoperative intubation time, length of hospital stay). In addition, follow-up data will be collected at 30 days and 6 months post-discharge, including variables such as need for readmission, further interventions, incidence of acute myocardial infarction, mortality, and variables related to PREM and PROM analysis.

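### The same secondary outcomes are timed from discharge in two sections and from surgery in a third, and the intervention is designed to change the interval between those origins

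*Protocol article*

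**What the plan says.** Three sections of the protocol article's Methods give a time origin for the follow-up outcomes.

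- **Follow-up:** "All patients included in the analysis will be followed up at 30 days and 6 months post-discharge". The stated purpose is "to assess hospital readmission rates, morbidity, patient-reported experience measures (PREM"), PROMs and mortality.
- **Database:** "follow-up data will be collected at 30 days and 6 months post-discharge, including variables such as need for readmission". Further interventions, myocardial infarction, mortality and the PREM and PROM variables are listed there too.
- **Outcomes:** the secondary outcomes include "comparison of morbidity, mortality rates, hospital readmissions, and assessment of PROMs and PREMs". The timing that this section gives for them is "between the intervention and control group at 30 days and up to 6 months after CABG".

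So two sections start the clock at discharge and one starts it at surgery, for the same set of outcomes. No section assigns different origins to different outcomes.

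The Outcomes section also says: "The primary outcome is the difference in postoperative length of stay between the intervention and control groups". The Sample size calculation section plans for a mean postoperative stay of 8.34 days under control and 5.56 days after intervention, each with SD 10.32.

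**The concern.** In many trials the difference between 30 days after surgery and 30 days after discharge is a loose use of words with little effect on the comparison. Here the interval between the two origins is the quantity the intervention is meant to shorten. If it works as planned, a window that is equal in both phases on one clock is unequal on the other.

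Readmission, morbidity and mortality are the outcomes that would show whether earlier discharge does harm. A modest artificial difference in either direction could be mistaken for harm or could hide it. If the origin is still open when data are seen, the choice can also be questioned afterwards.

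**Working it through.** **Inputs.** From the Sample size calculation section: mean stay 8.34 days (control) and 5.56 days (intervention), SD 10.32, two-sided 5% level, 80% power, N = 436 before losses and 240 per group after them. From the Follow-up, Database and Outcomes sections: windows of 30 days and 6 months. Six months is taken as 180 days.

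**The plan's own figure.** The difference is 8.34 − 5.56 = 2.78 days, and d = 2.78 / 10.32 = 0.269. A two-sided two-sample t-test at 80% power needs 217.3, rounded up to 218 per arm, so 436 in total. The stated figure is reproduced, and these are the stays on which the trial is planned.

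**Readmission.** A patient can be readmitted only after discharge. With a window of H days from surgery, mean time at risk is about H minus mean stay. With a window of H days from discharge it is H in both phases.

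| Window | Control | Intervention | Ratio |
|---|---|---|---|
| 30 days from surgery | 30 − 8.34 = 21.66 | 30 − 5.56 = 24.44 | 1.128 |
| 30 days from discharge | 30 | 30 | 1 |
| 180 days from surgery | 180 − 8.34 = 171.66 | 180 − 5.56 = 174.44 | 1.016 |
| 180 days from discharge | 180 | 180 | 1 |

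**Deaths and complications counted from the operation.** With a cut-off H days after surgery, the time covered is H in both phases. With a cut-off H days after discharge it is H plus mean stay.

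| Cut-off | Control | Intervention | Ratio |
|---|---|---|---|
| 30 days after surgery | 30 | 30 | 1 |
| 30 days after discharge | 30 + 8.34 = 38.34 | 30 + 5.56 = 35.56 | 0.927 |
| 180 days after surgery | 180 | 180 | 1 |
| 180 days after discharge | 180 + 8.34 = 188.34 | 180 + 5.56 = 185.56 | 0.985 |

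**Skewness.** The SD exceeds both means, so some stays will pass 30 days, and time at risk cannot be negative. Averaging max(30 − stay, 0) over distributions with the plan's means and SD gives a ratio of 1.122 (lognormal) or 1.126 (gamma). The 13% is therefore barely affected.

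**Effect on event proportions with no true treatment effect.** The article gives no event rates, so these are assumptions. With a constant daily hazard h = −ln(1 − p)/30, the proportion with an event by time t is 1 − exp(−h t).

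- *Readmission by 30 days from surgery.* For p = 5% per 30 days at home: 3.6% control and 4.1% intervention. For p = 20%: 14.9% and 16.6%. The intervention phase looks about 12% worse in relative terms, or about 1 to 4 patients per 240.
- *Mortality from surgery to 30 days after discharge.* For 30-day mortality of 2%: 2.55% control and 2.37% intervention. For 5%: 6.35% and 5.90%. The intervention phase looks about 7% better in relative terms, or about 0.4 to 1.1 deaths per 240.

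**The case against.** The strongest reply is that the sections do different jobs. Follow-up and Database would say when the telephone calls are made, and Outcomes would say what is compared. Calls made 30 days and 6 months after discharge always fall after the same points counted from surgery, so dated events can be re-windowed. Exact windows may also stand in the full protocol, an analysis plan, the schedule figure or the supplementary table, none of which is shown. This reading is possible and it makes the repair cheap. It does not remove the conflict, because the article never draws that distinction and attaches the same outcomes to both origins. Nor does it help PROM and PREM scores: they are measured at the call and cannot be moved to another time point afterwards.

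Two stronger readings are tempting, and the documents support neither.

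- **That in-hospital deaths are excluded.** A patient who dies before discharge has no discharge date from which to count, so a reader might infer this. But the Database section adds the calls to postoperative data, including complications, that are already collected, and a mortality rate after CABG naturally includes deaths in hospital. What is unstated is which window counts them.
- **That the two origins bias a given comparison in opposite directions.** For each outcome one origin gives equal time and the other is tilted. The direction differs between outcomes: the surgery origin works against the intervention for readmission, and the discharge origin favours it for deaths and complications counted from surgery.

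It is also fair to say that the expected shifts amount to a few patients at most and leave the primary outcome and sample size untouched.

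**Conclusion.** The contradiction is plain in the text and should be reconciled. Its consequence is real but modest. At the planned stays, the less suitable origin creates about a 13% imbalance in time at risk for 30-day readmission, or about a 7% imbalance in the time covered for deaths and complications. At 6 months either imbalance is about 1.5%. Only secondary outcomes are affected.

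The time-at-risk ratios rest on the intervention reaching its target; a smaller reduction in stay gives a smaller imbalance. The event proportions also rest on assumed rates and a constant hazard. If risk is higher soon after surgery, the true distortions will differ from those shown. Equal time at risk also does not mean equal risk: on the discharge clock, the intervention phase's readmission window starts earlier after surgery. Confidence is high in the contradiction and in the time arithmetic, and lower in the event counts.

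**What to change.** Align the three sections and state one origin for each outcome:

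- **Mortality and morbidity:** count from surgery to day 30 and day 180, and say explicitly that in-hospital events are included.
- **Readmission:** count from discharge, where both phases have equal time at risk. If the window is kept from surgery, the analysis should account for the unequal time at risk.
- **PROMs and PREMs:** state that they are timed from discharge, as the calls are.

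The calls can stay as scheduled, provided that the date of each death, complication and readmission is recorded. Days alive and out of hospital could be added as an optional supplement, but it includes the index stay: a stay shorter by 2.78 days raises it even if readmissions worsen. It should therefore not replace readmission.

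The cost is a wording change in three sections and event-date fields on the call form if they are not already there. No extra contacts and no change in sample size are needed. The article reports that recruitment is under way, so the change is best made before any outcome is compared by phase.

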## Discussion

CABG is a primary therapeutic approach for treating coronary artery disease and one of the most performed and studied cardiac surgeries worldwide [34]. Despite ongoing technical and scientific advancements aimed at improving outcomes [2,35,36], prolonged hospital stay after surgery remains a significant challenge for healthcare teams who seek continuous improvement in patient care. In Brazil, the average length of stay after CABG in 2021 was 11,8 days [37], incurring an estimated cost of approximately 1 billion reais [38].

Factors such as inadequate preoperative preparation, disconnected care protocols, and decision-making based on outdated concepts are related to prolonged hospital stay, negatively affecting the patient experience and increasing the risk of complications, ultimately impacting prognosis [6,39–41]. Studies indicate that extended hospitalization is associated with higher rates of postoperative morbidity and mortality, in addition to imposing a financial burden on healthcare institutions [6,7,42–44].

Despite the proven benefits of optimized recovery pathways, their implementation in cardiac surgery is still rare and inconsistent, due to barriers related to interdisciplinary team interaction and communication [45–47]. In Brazil, a pioneering group developed first series of cases based on the Enhanced Recovery After Surgery concept, in the STS EACTS LATAM conference in 2019 [48], the same year that ERAS published its first guideline for cardiac surgery (ERACS) [24]. A subsequent detailed analysis of this series reported a median postoperative length of stay of 3 days while maintaining quality and safety standards and reducing negative outcomes [1]. However, the study also highlighted challenges related to adherence to metrics and effective communication among healthcare teams.

The use of a mobile application can improve adherence to protocols by facilitating communication and monitoring of metrics, while optimizing the journey of patients undergoing CABG [13,14] and procedures in other specialties [47–49]. Successful implementation requires involvement from hospital management and comprehensive staff training. The mobile device application is presented as a tool that humanizes the use of technology, facilitating the educational content delivery to patients, enhancing communication among healthcare professionals, and providing a comprehensive view of the patient’s trajectory during hospitalization. Patient familiarity with mobile devices and internet use was considered as inclusion criteria to ensure intervention adherence. In contrast, a previous study [49] suggested that technology may not improve adherence to enhanced recovery protocols for colorectal surgery. It is important to point out that the study had varying patient assistance needs, lack of blinding, and inpatient-only data collection.

In this scenario, the Kamay application significantly supports the project, distinguishing itself from other available apps. A user-friendly design that combines text, videos and images, aiming to engage and educate patients and relatives for the perioperative phase, as well as pre- and post-rehabilitation. The professional module maps the entire perioperative cycle, categorizes patients according to their care stage, enables process checklists, alerts unmet targets and tracks key ERAS-based activity metrics, features that enhance adherence and sustainability of the care model, reducing manual workload and interpersonal strain, minimizing repeated reminders from hospital leadership. By connecting multiprofessional teams, patients and their families in real time, the platform fosters engagement that ERAS protocols alone cannot achieve. Lastly, the activity management dashboard compiles all input data into real-time graphs and reports, supporting continuous data analysis and process improvement. The modular design and dynamic updates across hospitalization stages promote transparency and shared responsibility, favoring the dissemination of an ERACS culture in daily practice.

In 2024, Dou et al. [50] published a research protocol with similarities to the proposed project; however, it did not incorporate technological resources during the intervention period. The inclusion of digital tools in our study is critical, as evidence shows that the use of applications and platforms can enhance care quality, reduce complications, and generate cost savings [14]. By integrating technology, our modernizes the approach, enabling real-time monitoring and personalized support. Technology represents the future of medicine and aligns with current trends in healthcare innovation [14].

The study will be conducted using a stepped-wedge cluster randomized design, as used by Dou et al. [50], which allows for gradual evaluation of the intervention and is particularly well-suited for service delivery interventions. This model effectively balances robust assessments with logistical limitations and reduces biases since the same clinical team treat the REPLICCAR patients during both the control and intervention phases [51]. The choice of a stepped-wedge design was also based on the well-established effectiveness of rapid recovery care pathways, which are supported by strong scientific evidence. Given this context, a traditional parallel cluster randomized trial was considered ethically inappropriate.

In view of this, our hypothesis is that the optimized recovery concept, based on the ERAS framework and combined with a real-time monitoring application, has the potential to significantly reduce hospitalization times for patients undergoing CABG surgery at major centers in the state of São Paulo, by increasing adherence to care protocol metrics. The post-pandemic context presents a favorable scenario, characterized by a repressed demand of at least 150% [52,53], which could decrease hospital exposure risk and reduce consumption of resources, while increasing bed turnover, and expanding access to healthcare within the Brazilian Unified Health System.

Given the significant challenges faced by many low- and middle-income countries (including resource limitations and patient population), the findings of this study may have relevance beyond the Brazilian context. If the hypothesis is confirmed, implementing the *Tempos Certos* enhanced recovery pathway for CABG surgery, adapted for the Brazilian context [48], associated by a digital heath tool as the Kamay app, could serve as a scalable model to improve results in diverse settings, although future research will be needed to explore its adaptation and feasibility.

After the advancements achieved through the creation and development of the REPLICCAR I and REPLICCAR II [31] databases, REPLICCAR represents an unprecedented study in CABG. This study aims to demonstrate that the use of a health application associated with an optimized recovery care protocol can reduce postoperative length of stay for patients undergoing CABG in the state of São Paulo, thereby providing greater quality and safety of treatment for individuals with cardiovascular diseases in the state.
